## Abstract

**Background:**

Traditional treatment for motor impairment after stroke includes medication and physical rehabilitation. The transcranial direct current stimulation associated with a standard physical therapy program may be an effective therapeutic alternative for these patients.

**Methods:**

This study is a sham-controlled, double-blind, randomized clinical trial aiming to evaluate the efficacy of transcranial direct current stimulation in activities of daily living and motor function post subacute stroke. In total there will be 40 patients enrolled, diagnosed with subacute, ischemic, unilateral, non-recurring stroke. Participants will be randomized to two groups, one with active stimulation and the other with a placebo current. Patients and investigators will be blinded. Everyone will receive systematic physical therapy, based on constraint-induced movement therapy. The intervention will be applied for 10 consecutive days. Patients will undergo three functional assessments: at baseline, week 2, and week 4. Neuropsychological tests will be performed at baseline and week 4. Adverse effects will be computed at each session. On completion of the baseline measures, randomization will be conducted using random permuted blocks. The randomization will be concealed until group allocation.

**Discussion:**

This study will investigate the combined effects of transcranial direct current stimulation and physical therapy on functional improvement after stroke. We tested whether the combination of these treatments is more effective than physical therapy alone when administered in the early stages after stroke.

**Trial registration:**

NCT02156635 - May 30, 2014. Randomization is ongoing (40 participants randomized as of the end of December 2015).

## Background

A stroke is defined as an acute neurological dysfunction of vascular origin, with sudden development of clinical signs of brain function disorders, lasting more than 24 h [1].

In this sense, new therapeutic modalities have been developed for monitoring patients after a stroke [2]. Simis et al. [3] conducted a placebo-controlled clinical trial and found that transcranial magnetic stimulation (TMS) and transcranial direct current stimulation (tDCS) can cause increased hand motor function compared to placebo stimulation. TMS has been used to minimize the limitations post stroke, such as functional independence and motor recovery [4, 5], but it is not portable/mobile and is expensive. In contrast, tDCS offers some advantages compared to TMS, being portable, more economical, and easy to operate. The effects are polarity-dependent, leading to an increase or a decrease in cortical excitability [6]. Although some studies have shown that increasing the current intensity is related to more robust effects [7], this is also true for adverse effects such as headache and discomfort under the electrode [8]. Therefore, the maximum current intensity used is generally 2 mA, and the cortex density varies between 0.029 and 0.08 mA/cm^2^ [9]. Animal studies with a higher current density of 25 mA/cm^2^ did not induce lesions in the brain tissue, meaning that limits well above those applied in humans did not result in potential adverse effects [10], thereby demonstrating that it is a safe technique.

There is evidence that repeated sessions of tDCS may be associated with a longer duration of the behavioral effects [11]. Monte-Silva et al. [12] demonstrated that the interval between the sessions can be critical to performance. The authors found that when an extra session of tDCS is applied for 1 hour after the first session, the effects last for a longer time (120 minutes) compared to the effect of only one or two consecutive sessions, while an extra session of tDCS applied beyond that period (that is, 3 hours) did not influence the effect of the first session. These findings show that studies with the aim of achieving lasting effects should consider the timing-dependent plasticity stimulation regulation in the human motor cortex [13].

Regarding physical therapy, different approaches can be found for motor recovery, such as mirror therapy [14], repetitive task practice [15], and robotic training [16]. However, the type of training that is combined with stimulation determines how generalizable the benefits would be. Improvements are specific for tasks that are strategically paired with stimulation [17].

In this perspective, efforts are currently being made to standardize the application of the methods that can be combined with tDCS for the treatment of stroke. Bolognini et al. [18] developed a placebo-controlled trial to investigate the neuropsychological and behavioral effects of bihemispheric tDCS (cathodic stimulation in the unaffected hemisphere and anode in the affected cortex) combined with a standard physical therapy program called constraint-induced movement therapy (CIMT) [19]. The data show that CIMT applied alone only seems to be effective in modulating cortical excitability, but is not able to restore the balance of transcallosal inhibition. According to the authors, bihemispheric tDCS can already achieve this goal and promote greater functional recovery. Studies show that CIMT is associated with functional improvement in acute and subacute stages of stroke [20–23]. Although most studies in neurostimulation therapy involve post-stroke patient monitoring for short periods [24, 25], longitudinal studies would clarify the action mechanisms and the effective duration of this association (tDCS plus CIMT) from the early stages of stroke.

The effectiveness of stroke interventions is often described by measures of disability, or functional assessment. Evaluations that deal with activities of daily living (ADLs) generally include the Functional Independence Measure, the Katz index and the Barthel index (BI), the latter being a prevalent measure for the clinical evaluation of stroke patients, with substantial supporting research [26–28]. However, there are few studies involving the ADLs as the primary outcome for a marker of functional recovery after neurostimulation. For example, in a systematic review where the efficacy of tDCS in ADLs and motor function after stroke were analyzed, the authors found that the results are inaccurate and the effect was not sustained when studies of high methodological quality were included. There were 15 studies involving a total of 455 participants included, with only randomized controlled trials and randomized controlled cross-over trials evaluated. Of the total, the analysis of five studies involving 286 participants to examine the effects of tDCS on our primary outcome (ADLs evaluated by BI) has shown that no effect was observed on the performance at the end of the intervention. In three studies from this systematic review involving 99 participants to evaluate the effects of tDCS in BI scores at the end of follow-up, evidence suggested an effect on the ADL performance, but the confidence intervals were wide, and the effect was not sustained when they only included studies with low risk of bias. Thus, the authors point to the need for future research in this area to improve the generalization of the results [29].

Although clinical trials can be found that measure the efficacy of tDCS in ADLs pointing to positive effects [30, 31] among other factors, in general they only include participants in the chronic stage with brain injuries in different areas and varying levels of functional incapacity.

Therefore, central questions remain: For a daily protocol of 10 days, does the active tDCS applied under a 2 mA current and associated with CIMT have a superior response to the simulated (placebo) current applied with CIMT, and if so, what is the size of the effect? What adverse effects are associated with the therapy? Does functional improvement in the ADLs persist over time?

In light of this, a clinical trial phase II/III will be developed to evaluate the therapeutic effects of tDCS in patients in the subacute stage after stroke. The purposes are two: 1) discuss topics related to safety, adverse effects, feasibility, and effectiveness of tDCS in the treatment of stroke patients; 2) present the work protocol prior to clinical trial results, ensuring adherence to protocol. Our hypothesis is that the active stimulation in the affected hemisphere is more effective than a simulated (placebo) current in activities of daily living in subacute stroke. Secondly, we are interested in knowing whether tDCS is effective in the recovery of the following motor variables: spasticity, use of the affected limb, balance, posture, fall risk, muscle strength, and upper and lower limb function. Also, we aim to analyze if a possible functional improvement produces a change in the patients’ perception of their quality of life. We hope that the study will contribute to the discussion of the methodological procedures of clinical trials phase II/III involving neuromodulation for the treatment of patients after stroke.

## Methods

### Overview

This is a placebo-controlled, double-blind, randomized clinical trial (Fig. 1), in which 40 patients are divided into two groups of 20 participants each. In Fig. 1, the CONSORT (Consolidated Standards of Reporting Trial) flowchart [32] shows the number and distribution of participants: Group A1 - participants in post-stroke subacute stage that receive active tDCS combined with CIMT; Group A2 - participants in the post-stroke subacute stage who receive a placebo stimulation associated with CIMT. Patients will undergo three assessments: baseline (T0), week 2 (T1), and week 4 (T2). Neuropsychological tests will be performed at T0 and T2. Adverse events will be measured in each session, where the researcher responsible for administering the neurostimulation will question the patient on whether they experience any uncomfortable or painful sensation, and if this is related to the tDCS, following the procedure of Brunoni et al. [33]. At the end of the study, participants who received tDCS and showed clinical improvement will be invited to receive bimonthly stimulation for 12 months as part of a longitudinal study of tDCS for stroke. Those who received the tDCS placebo and did not respond will be invited to receive daily sessions with an active current for 10 days. Finally, those who had a response to the placebo will be referred for other physical therapy treatment.

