### Randomization and blinding

The method of randomization will be a 1:1 permuted block randomization generated by a web-based randomization tool (www.random.org). This sequence will be done independently and remotely by a blinded investigator who will not have contact with other research procedures. The randomization will be concealed until group allocation.

After the randomization process, a blind researcher not involved with the recruitment, data collection, or intervention will perform the allocation of participants between the groups. This will be employed by concealed allocation of sequentially numbered, opaque, sealed envelopes, so that the person responsible for allocation will not have contact with patients or with the work of others. This envelope will be delivered one day before the treatment sessions to the researcher responsible for neurostimulation, who will not be involved with the other procedures for collection or data analysis.

Participants will not be identified by their real names and will not be aware of which arm of the study they are allocated to. When included in the study, they will receive a sealed, opaque envelope containing their respective identification code. In this way, the assessors will also be blind, as they will be identifying the patients by codes and will not have contact with other research procedures. The same will happen to the staff responsible for the execution of CIMT procedures. Data analysis will be conducted by a researcher not involved in any stage of recruitment, screening, assessment, or intervention.

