### tDCS

The planning of the stimulation variables involves intensity, frequency of sessions, size/position of the electrodes, and duration of treatment [9]. The review of the therapeutic use of tDCS which defined safety variables was based on 21 studies (n = 278), and the conditions included depression, Parkinson’s disease, cerebral ischemia, eating disorders, alcohol dependency, and chronic pain syndromes. The application of an anodic current with identical variables to this study (involving the use of 35 cm^2^ electrodes and applying a current of 2 mA for 20 minutes for 10 days) was not related to long-term adverse or high magnitude effects [81].

The electrodes are positioned on the participant’s head at the primary motor cortex area, C3 or C4 position according to the electroencephalogram 10–20 system [82]. The anode is placed on the affected hemisphere and the cathode (reference electrode) on the supraorbital region in the uninjured hemisphere [83].

The protocol will be for 20 minutes of stimulation for 10 days (excluding weekends). The TCT neurostimulator (Research Version) developed by Trans Cranial Research Limited (Hong Kong, China) will be used, with the kit containing the neurostimulator, sponges, rubber fasteners, electrodes, and connecting cables. Electrodes are encased with 5 × 7 cm sponges and moistened with saline (0.9 % NaCl). The applied current is 2 mA, with a relative current density of 0.05 A/m2.

The protocol is identical for placebo stimulation, but the current will stop after 30 seconds from the start of stimulation, a blinding method considered reliable for several previous studies [9, 84], in which the active current is simulated (slight tingling and itching sensation) for a short period, and the effects disappear shortly after the start of the stimulation.

Although the required number and maximum sessions have not been established, we prefer to follow the model used in previous studies, which for most cases had consecutive sessions of tDCS applied for 10 days, and was able to improve motor function in different phases of stroke [24, 85, 86].

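### Session adverse effects are elicited by the researcher who receives the allocation, although the abstract states that investigators are blinded

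*Protocol article*

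**What the plan says.** Overview: at every session "the researcher responsible for administering the neurostimulation will question the patient on whether they experience any uncomfortable or painful sensation". The same sentence has this researcher ask whether the sensation is related to the stimulation.

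Randomization and blinding: "This envelope will be delivered one day before the treatment sessions to the researcher responsible for neurostimulation". The sentence goes on to describe this researcher as one "who will not be involved with the other procedures for collection or data analysis". Of the outcome assessors the section says that "the assessors will also be blind, as they will be identifying the patients by codes and will not have contact with other research procedures", and it extends this to the staff who deliver the physical therapy (CIMT). The data analyst is described as someone with no part in recruitment, screening, assessment or intervention.

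tDCS: sham follows the active procedure, except that "the current will stop after 30 seconds from the start of stimulation".

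Abstract, Methods: "Patients and investigators will be blinded". The Overview also calls the trial double-blind. Neither statement makes an exception for the person who stimulates.

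Safety: patients are asked about named symptoms and score their intensity from 1 to 4. Relation to stimulation is scored from 1 to 5.

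Data analyses: adverse effects are compared between groups by Fisher's exact test, and they are one of the factors in the logistic regression on correct guessing of allocation.

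**The concern.** Tingling, sleepiness, headache and the like are subjective, and how often they are reported depends on how the question is put. A questioner who knows the arm may probe further, accept a vague answer sooner, or note a marginal complaint in one arm and not in the other, without meaning to. The questioning may also cue the patient about the allocation.

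Two planned analyses use these data. One is the between-arm comparison of adverse effects, which answers one of the central questions posed in the Background. The other is the check on blinding itself, where adverse effects are a predictor of a correct guess. A person whose questions could reveal the arm would thus supply a predictor for the analysis meant to detect that the arm was revealed.

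A reader of the abstract would take the adverse-effect data to have been collected blind, and the methods do not provide for that.

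**Working it through.** The point rests on no figure in the plan, so the main check sets the sections side by side.

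**Who knows the arm**

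| Role | What the article says | Knows the arm? |
|---|---|---|
| Patient | Not aware of the arm | No |
| Sequence generation, allocation | Each done by a blinded researcher | Described as no |
| Outcome assessors, CIMT staff | Blind, work by codes | No |
| Data analyst | Not involved in the other stages | Independent; not called blind |
| Stimulation researcher | Receives the envelope, delivers active or sham current | Yes, by inference |

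The inference for the last row has two parts. The envelope that carries the allocation goes to this person. This person also runs either 20 minutes of current or a current that stops after 30 seconds, and no coded or automatic sham mode is described. The article never says outright that this researcher is unblinded, but it offers no other reading.

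**Who collects session adverse effects**

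The Overview names the stimulation researcher as questioner. No section gives the questioning or the recording to a blinded person. The abstract's statement that investigators are blinded therefore fails for the one investigator who questions patients about session symptoms.

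**How much data is exposed**

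40 participants × 10 sessions = up to 400 interviews.

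**Could unequal recording matter at this sample size?**

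The article gives no adverse-effect rates, so the following uses assumed values and shows scale only. Assume 20 per group all analysed, the same true proportion p with an effect in both arms, every effect recorded in one arm, and only a share s recorded in the other. The probability that the two-sided Fisher test rejects at 0.05 is

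Σ Bin(a; 20, p) × Bin(b; 20, s·p), summed over all pairs (a, b) with a Fisher p-value of at most 0.05.

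| True rate p | s = 1 | s = 0.8 (recorded rates) | s = 0.6 (recorded rates) |
|---|---|---|---|
| 30% | 2.5% | 3.7% (30% v 24%) | 8.2% (30% v 18%) |
| 50% | 2.0% | 4.9% (50% v 40%) | 16.3% (50% v 30%) |
| 70% | 2.5% | 9.1% (70% v 56%) | 30.4% (70% v 42%) |

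The result is the same whichever arm is under-recorded. The same mechanism could hide a true difference.

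**The case against.** The strongest reply has five parts.

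- **Role separation.** A reader might infer that the Overview flatly contradicts Randomization and blinding, which keeps the stimulation researcher out of other data collection. The text does not support that as fact. The word *other* can be read as excluding only tasks beyond this researcher's own session, and questioning about symptoms belongs to that session. The two sections sit uneasily together but can be reconciled. The conflict with the abstract remains on either reading.
- **Who rates.** Intensity and relation are scored by the blinded patient, in answer to named symptoms. This stands. It narrows the exposure to prompting, cueing and recording.
- **Size.** In the illustration, 20% under-recording in one arm leaves the rejection rate below 5% in two of three cases. Larger inflation needs 40% under-recording, for which the article gives no basis. This also stands, so one cannot say that the comparison is biased, only that it is open to bias.
- **Necessity.** The operator is with the patient and has to notice strong discomfort in any case. That is a reason for the operator to ask about urgent events, not for the operator to be the source of the comparative data.
- **Already disclosed.** Randomization and blinding largely sets out the roles, so a careful reader can work out who is unblinded. Even so, the abstract is unqualified and nothing in the methods corrects it.

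The Overview also cites the procedure of an earlier trial. Nothing in the article shows that the questioner in that trial knew the arm.

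**Conclusion.** The concern holds in a limited form. The abstract's blinding statement is wrong for the stimulation researcher, and that researcher elicits all session adverse-effect data, up to 400 interviews. The conclusion rests on one inference, that receiving the envelope and delivering active or sham current means knowing the arm.

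What is at risk is the session symptom data, and through them the Fisher comparison and the regression on correct guesses. A reader might extend this to the whole safety analysis or to the primary result. The article does not support that: assessors described as blind rate the outcomes, including the Barthel index, and the cognitive tests are not assigned to the stimulation researcher. Neither the direction nor the size of any bias can be derived from the document.

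The point deserves correction because adverse effects are a stated aim and the remedy is cheap. It does not threaten the primary analysis.

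**What to change.** 1. **Collection.** Put the symptom list and the two scales from the Safety section on a one-page form under the participant's code, with fixed wording identical in both arms. The patient scores it after each session and seals it, and only the data analyst opens it. The stimulation researcher still records events that need immediate action.
2. **Help with writing.** The helper should be neither an outcome assessor nor CIMT staff, and should not know the arm. Symptom reports could hint at the allocation, and the article says that assessors have no contact with other procedures. Where no such person is available, the stimulation researcher reads the fixed script word for word.
3. **Blinding statement.** Reconcile the abstract, the Overview, and Randomization and blinding. State that participants, assessors and CIMT staff are blinded, that the analyst is independent of the other trial stages, and that the stimulation researcher is not blinded.
4. **Sessions already held.** Trial status reports 40 participants randomized by the end of December 2015. For completed sessions, report how adverse effects were collected, and by whom, as a limitation of the safety comparison and of the blinding regression.

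The cost is one form, a change of wording, and help for participants with poor hand function. That help may be needed often, since every participant trains a paretic arm while the other is restrained for most of the waking day.
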